### **3.10 Data Safety & Monitoring Board (DSMB)**

The DSMB will comprise physicians & nurses familiar with the study but not participating as investigators or employed at any of the study sites. The DSMB will meet on an ad hoc basis and as needed to perform its various functions. Most meetings will be by conference telephone call or by electronic mail conference. The DSMB will have the following functions and the study will follow the following data safety plan:

- a. Review of all Adverse Event (AE) and Serious Adverse Event (SAE) reports. Such review will occur within 10 days of receipt of an AE report and within 24 hours of receipt of an SAE report. The DSMB will make an independent determination as to whether each SAE was likely related or unrelated to the study medications or procedures and will make a determination as to whether the group assignment code ought to be broken to further evaluate the event.
- The principal investigator or designee at each study site is responsible to report any SAE to the Obstetrix Center for Research & Education (CRE) and to the DSMB within 24 hrs of recognition of the event. The report will be made using a standardized form submitted by fax or by e-mail to the study coordinator. SAE's include these events:
  - (i) Anaphylactic reaction or other life-threatening reaction to injection of study medication (17P or placebo)
  - (ii) Injection site infection requiring incision & drainage or IV antibiotic therapy
- The principal investigator or designee at each study site is responsible to report any AE to the Obstetrix CRE and to the DSMB within 10 days. The report will be made

using a standardized form submitted by fax or by e-mail to the study coordinator.

AE's include these events:

- (i) Injection site infection treated with oral antibiotics
  - (ii) Pain or other symptom at injection site that causes the mother to discontinue further injections.
- Neonatal morbidity events attributed directly to preterm delivery and/or to perinatal infection are specifically excluded from the list of adverse events. Indeed, such events are common & expected in patients with PROM. They comprise an important set of endpoints in this trial. Their frequency will be analyzed with the tertiary hypothesis. Such events include, but are not necessarily limited to:
  - (i) death of newborn born at gestational age 28w0d or less
  - (ii) respiratory distress syndrome (RDS)
  - (iii) intracranial hemorrhage (ICH)
  - (iv) necrotizing enterocolitis (NEC)
  - (v) positive newborn blood culture
  - (vi) suspected neonatal sepsis
- Similarly, maternal morbidities known to be associated with PROM are specifically excluded from the list of adverse events. Such events include:
  - (i) prolonged hospitalization
  - (ii) intraamniotic infection
  - (iii) placental abruption

b. Planned interim analysis. Upon receipt of 50% of the CRF's (111 participants total), the DSMB will conduct an interim analysis of the efficacy & safety results. The primary outcome will be compared between the treatment groups to determine if there is a significant difference. The frequency of SAE's and AE's in the two groups (17P vs. placebo) will also be compared. Based on the results of this analysis, the DSMB will make a determination whether the trial should continue. The trial will be discontinued if any one of the following is found:

- (i) A significant between-group difference is found in the proportion of participants with the primary outcome measure. At the interim analysis (50% of participants), significance is defined as  $\alpha = 0.0031$ .
- (ii) It seems extremely unlikely that continuation of the trial will disclose a significant difference based on the conditional probability analysis.
- (iii) There is a safety concern, such as significantly higher rate of AE's, SAE's, or neonatal morbidity in the 17P group.

If the trial is discontinued, all enrollment & randomization of new participants will be immediately halted. A final data analysis will be completed after the CRFs have been submitted from all randomized participants. If the trial is continued, the details of the interim analysis will not be made available to the site investigators, but a summary report will be issued to the site investigators stating that the DSMB concluded that continuation of the study was warranted.

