### **3.12 Compliance with Regulations & Conventions**

To protect the rights and welfare of participants, the study will be conducted in conformance with the Declaration of Helsinki, applicable FDA guidelines, the ICH E6 guidelines on Good Clinical Practice (GCP), and/or the laws and regulations of the participating country, whichever affords the greater protection to the human participant.

All investigators, sub-investigators and study personnel are required to read and follow the protocol, as well as any literature that accompanies the products prior to conducting the study procedure for the first time. All investigators participating in this study will be required to be trained in the proper use of the study procedures and in the components of this protocol by the sponsor.

The PI is ultimately responsible for the conduct of this study; however, he/she may designate a member of his/her staff to assist with the collection of data and completion of CRFs. The designee(s) will be documented on an authorization form that is signed by the PI and kept in the Regulatory Binder, to be updated as necessary.

Obtaining informed consent in accordance with national policy is mandatory for participant participation. All participant data is kept confidential and procedures will be implemented to ensure that participant confidentiality is not compromised. If alternative consent materials are used, they must be approved by Obstetrix CRE and the IRB at the clinical site prior to use. Documentation of the approved informed consent must be provided to Obstetrix CRE prior to study commencement at the clinical site.

After Informed Consent has been obtained, all screening procedures have been performed, and eligibility for the study has been confirmed, the participant will be considered enrolled in the study. After this point, the reason(s) must be documented on the CRF for any participant who withdraws, or for any reason cannot complete this study.

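### Protocol section 3.10a leaves stillbirth, newborn death after 28w0d and maternal death without a clear place in 24-hour SAE reporting and case-level DSMB review

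*Protocol*

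**What the plan says.** Section 3.10a requires sites to report any SAE to the coordinating centre and the DSMB within 24 hours, and any AE within 10 days. For each SAE the DSMB judges relatedness and decides whether to break the code.

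- **SAEs.** The list opens with "SAE's include these events" and has two items: "Anaphylactic reaction or other life-threatening reaction to injection of study medication (17P or placebo" and "Injection site infection requiring incision & drainage or IV antibiotic therapy".
- **AEs.** The list opens with "AE's include these events" and has two items: "Injection site infection treated with oral antibiotics" and "Pain or other symptom at injection site that causes the mother to discontinue further injections".
- **Neonatal exemption.** Neonatal events attributed directly to prematurity or perinatal infection are not adverse events. The examples are stated to be non-exhaustive, and the first is "death of newborn born at gestational age 28w0d or less".
- **Maternal exemption.** Morbidities known to accompany PROM are not adverse events. Prolonged hospitalization, intraamniotic infection and abruption are named.

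Section 3.10b plans one DSMB analysis of efficacy and safety, on receipt of 111 CRFs. A higher rate of AEs, SAEs or neonatal morbidity in the 17P group is a ground for stopping. Section 3.7 counts stillbirth, neonatal death and infant death before discharge as components of composite neonatal morbidity, at any gestational age.

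**The concern.** The reporting rules cover what the needle might do, not the gravest outcomes of the pregnancy. A 28-week cut-off on exempt deaths makes sense only if some later deaths are meant to be reported, yet nothing on the reportable side receives them. Stillbirth and maternal death are on neither side.

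Three safeguards depend on an event being classed as an SAE: 24-hour review, the DSMB's relatedness judgement and the decision to unblind. So does the comparison of SAE rates by arm at the interim. If sites classify the same death differently, that comparison loses meaning for fatal events.

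This matters because section 2.5 says the investigators know of no completed or ongoing trial of 17P in PROM. Section 2.2 says that continuing the pregnancy, which is the intended effect, carries risks of infection, abruption and cord accident that can kill the offspring.

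**Working it through.** No stated figure is in dispute. The check places each type of death against every list and route in sections 3.7, 3.10a and 3.10b.

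| Event | SAE or AE list | Exemption | Study outcome (3.7) | Route to the DSMB |
|---|---|---|---|---|
| Newborn death, born at 28w0d or earlier | Not named | Named | Yes, in composite | Interim, as neonatal morbidity |
| Newborn death, born after 28w0d | Not named | Not named; could be read in | Yes, in composite | Interim, as neonatal morbidity |
| Stillbirth | Not named | Not named | Yes, in composite | Interim, as neonatal morbidity |
| Maternal death | Not named | Not named | No | None stated |

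**Two readings of one case.** Take a newborn born at 30 weeks who dies of a complication of prematurity. By the cut-off, the death lies outside the named exemption, so it should be reportable, but under no listed item. By the cause-based rule with its open-ended examples, the death is attributed to prematurity and is exempt. Both readings follow from the text.

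**Timing of the composite route.** The interim covers 111 of 222 participants. No later look is planned for the other 222 − 111 = 111. Under section 3.11b a CRF copy may follow up to 30 days after delivery and discharge of mother and infant, against 24 hours for an SAE.

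**Content of the composite route.** Section 3.9 assumes composite rates of 60% (placebo) and 40% (17P). At the interim each arm has about 111 / 2 = 55.5 participants:

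- placebo: 55.5 × 0.60 = 33.3 with the composite;
- 17P at the design effect: 55.5 × 0.40 = 22.2;
- difference: 33.3 − 22.2 = 11.1.

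Suppose, for illustration only, that the whole design effect came from fewer non-fatal events. Extra deaths in the 17P arm, in offspring who would otherwise have had no component, would have to exceed 11 before the composite looked worse than on placebo. A death in an infant who already has RDS adds nothing to the count. This shows what the composite can hide; it does not forecast deaths. Section 2.2 gives no mortality rate. Among the complications it quantifies, respiratory distress is the largest (10–40%, against up to 5% for intracerebral hemorrhage and 2–6% for necrotizing enterocolitis), so a mainly non-fatal composite is the reasonable expectation.

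Section 3.9 does compare the component morbidities separately. Section 3.10b does not ask for deaths to be shown separately at the interim.

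**The case against.** The strongest reply is that the text closes less off than it seems to. Both reportable lists say what SAEs and AEs *include*, not what they are limited to, and sites must report any SAE. A careful investigator would surely report a maternal death. The DSMB meets ad hoc as needed and can ask for more. Fetal and newborn deaths are captured on the CRF and belong to the neonatal morbidity that the DSMB must weigh.

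Much of this stands, and it rules out four stronger readings:

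- A reader might infer that these deaths never reach the DSMB. For stillbirths and newborn deaths that is wrong, because of the interim route. For maternal death, the Protocol simply names no route.
- A reader might infer that the Protocol excludes these deaths from reporting. It does not say so; it leaves their classification open.
- A reader might see a breach of "the ICH E6 guidelines on Good Clinical Practice (GCP", cited in section 3.12, or of FDA rules. The Protocol reproduces no SAE definition from either, so a conflict cannot be shown from the document.
- A reader might size the problem from the share of births after 28w0d under the one-week half-life in section 2.2. That would be a share of births, not deaths, and would need an entry mix that the Protocol does not give.

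The reply does not close the gap. An open list with no criterion for what else belongs leaves each site to decide, and the neonatal exemption is equally open, so the two pull in opposite directions. An ad hoc board acts on what it is sent.

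**Conclusion.** The point holds as a gap in classification and should be fixed. Section 3.10a does not clearly place stillbirth, newborn death after 28w0d or maternal death under 24-hour reporting and case-level DSMB review, and its 28w0d cut-off is at odds with its open-ended exemption. Stillbirths and newborn deaths are seen by plan once, at 111 CRFs, within a composite that can move against them. Maternal death has no named route.

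The size cannot be put as a number of missed deaths, since the Protocol gives no mortality rates. The conclusion rests on the text of sections 3.7, 3.10a and 3.10b alone. The masking illustration also uses the 60% and 40% rates of section 3.9 and assumes that the benefit falls on non-fatal events. This is not left to a statistical analysis plan: section 3.10 is the trial's data safety plan, and section 3.11g requires exact adherence to the Protocol.

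**What to change.** 1. In section 3.10a, add maternal death, stillbirth and newborn death after 28w0d to the SAE list. Add a general criterion for any other fatal or life-threatening event not on the exempt lists. The criterion should not turn on length of maternal stay, because prolonged hospitalization is itself exempt.
2. Reconcile the 28w0d cut-off with the cause-based, non-exhaustive wording of the neonatal exemption, so that a given newborn death has one classification.
3. In section 3.10b, require that all deaths, including exempt ones, be tabulated by arm for the DSMB, separately from the composite.

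The cost is a few lines of Protocol text and some additional SAE reports. The document gives no basis for estimating how many. Other expected events of prematurity can stay exempt from expedited reporting.

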### **3.11 Ethical, Legal and Administrative Aspects**

a. Data Quality Assurance. Obstetrix research staff or their designee will conduct a site visit to verify the qualifications of each investigator, inspect the site facilities, and inform the investigator of responsibilities and the procedures for ensuring adequate and correct documentation.

Each investigator is required to prepare and maintain adequate and accurate case histories designed to record all observations and other data pertinent to the study for each study participant. All information recorded on the CRFs for this study, or on correction sheets (query forms or data clarification forms – DCFs) must be consistent with the participants' source documentation (i.e., medical records).

b. Case Report Forms and Source Documentation. All data obtained during this study should be entered on the study specific CRFs accurately and in a timely manner. All source documents from which CRF entries are derived should be present in the participant's medical records. During a monitoring visit, the original CRFs for each participant will be checked against source documents at the study site by the clinical site monitor.

Each CRF and DCF will consist of an original plus a copy. The copy will be forward to a designated person within the Obstetrix Research Team within 30 days of delivery and discharge of both mother and infant. The original will be kept at the site. Instances of

missing or un-interpretable data will be discussed with the investigator and study staff for resolution.

c. Access to Source Data and Monitoring. During the course of the study, a representative of Obstetrix Research team, or a designated representative [a Clinical Research Associate (CRA) or monitor] will make site visits as frequently as necessary to review protocol compliance, compare CRFs and individual participant's medical records, and ensure that the study is being conducted according to pertinent regulatory requirements. CRF entries will be verified with source documentation. The review of medical records will be performed in a manner to ensure that participant confidentiality is maintained.

It is the principal investigator's (PIs) obligation to ensure that documentation of all relevant data such as relevant medical history, date of study enrollment, visit dates, results of examinations or tests, and adverse events is correctly entered in the participant's file.

Checking of the CRFs for completeness and clarity, and cross-checking with source documents in the presence of the investigator or designee, will be required to monitor the progress of the study. Moreover, the FDA, IRBs, and/or the Sponsor's Clinical Quality Assurance group may wish to carry out such source data checks and/or on-site audit inspections. Direct access to source data will be required for these inspections and audits; they will be carried out giving due consideration to data protection and medical confidentiality. The investigator agrees to give the auditor access to all relevant documents for review. The same applies in case of an inspection by the authorities.

Obstetrix or designated representatives will affirm and uphold the principle of the subject's right to protection against the invasion of privacy. Throughout the study, all data will only be identified by participant number. Anonymity of the data will be maintained in all data analyses.

d. Archiving Study Records. According to ICH guidelines and FDA Regulations, essential documents should be retained for a minimum of 2 years after the last approval of a marketing application in an ICH region and until there are no pending or contemplated marketing applications in an ICH region or at least 2 years have elapsed since the formal discontinuation of clinical development of the investigational product. However, these documents should be retained for a longer period if required by the applicable legal requirements and/or local IRB/institutional requirement.

e. Good Clinical Practice. The procedures set out in this study protocol are designed to ensure that the Sponsor and investigator abide by the principles of the Good Clinical Practice (GCP) guidelines of the International Conference on Harmonization (ICH), and of the Declaration of Helsinki (2000, with clarification in 2004), and all applicable FDA Regulations. The study also will be carried out in keeping with local legal requirements.

f. Informed Consent. Prior to the administration of any tests or procedures required in this protocol, the investigator or designee will obtain informed consent in writing from all participants considered for entry into this study. Each participant, investigator or designee, and witness (as applicable) must personally sign and date the informed consent. Copies of the

informed consent will be retained in the medical record and the participant's study binder. A copy of the signed informed consent will be given to the participant to take home.

The consent form and as necessitated by local law, an additional participant information leaflet for study participation, will explain the nature of the study, its objectives and potential risks. Furthermore, it will detail the requirement of the participant, all trial procedures, alternative procedures and the fact that she is free to withdraw her consent at any time without reason. Details of indemnity and insurance are also stated.

As required by ICH-GCP the participant will give in writing her authorization that the study data may be given for review to the responsible authorities and that the monitor will be granted direct access to the participant's original medical records for verification of clinical data. The participant's information and ICF will be available in the participant's native language.

If a protocol amendment is required, the ICF will be revised if applicable to reflect the changes to the protocol. After the ICF is revised, it must be reviewed and approved by the appropriate IRB, and signed by all participants subsequently enrolled in the study as well as those previously enrolled in the study.

g. Protocol Approval and Amendment. Before the start of the study, the study protocol and/or other relevant documents will be approved by the IRB in accordance with local legal requirements. This protocol is to be followed exactly. To alter the protocol, amendments must

be written, receive approval from the appropriate personnel, and receive IRB approval prior to implementation (if appropriate).

Administrative changes (not affecting the participant benefit/risk ratio) may be made without the need for a formal amendment. All amendments will be distributed to all protocol recipients, with appropriate instructions.

h. Confidentiality. All study findings and documents will be regarded as confidential. The investigator and members of his/her research team must not disclose such information without prior written approval from the Sponsor.

The anonymity of participating participants must be maintained. Participants will be identified on CRFs and other documents submitted to the Sponsor by their participant number, initials and/or birth date, not by name. Documents not to be submitted to the Sponsor that identify the participant (e.g., the signed informed consent) must be maintained in confidence by the investigator.

i. Publication. At the conclusion of the study, a multi-center (if applicable) publication of the primary study outcomes will be prepared for publication in a reputable scientific journal. The analysis of other pre-specified and non pre-specified endpoints will be performed by Obstetrix Research Group's designated data management team.

j. Site Training. All investigators and appropriate study staff will be required to participate in a site training (or initiation if appropriate) to provide orientation and training regarding the applicable procedures, protocol and CRFs.

k. Required Reports. The following reports are required of the investigator:

- i. Reports to the Obstetrix CRE of any SAEs immediately or at least within 24 hours of the study site becoming aware of such events
- ii. Report to the Obstetrix CRE, within 72 working days, of withdrawal of approval by the reviewing IRB or regulatory authority
- iii. Report to the Obstetrix CRE and the reviewing IRB of any deviation from the protocol to protect the life or physical well being of a participant in an emergency situation. Such notice will be given as soon as possible, but in no event later than 5 working days after the emergency occurred
- iv. Reports of any study procedure(s) being performed without prior written informed consent being obtained. Such notice will be given to the Obstetrix CRE and the reviewing IRB within 10 working days of the study procedure(s) being performed
- v. Final report submitted to the Obstetrix CRE and the reviewing IRB as soon as possible, but no later than 3 months, of the conclusion of the study or the conclusion of the investigator's participation in the study
- vi. Other reports to the reviewing IRB as may be required

### **3.12 Compliance with Regulations & Conventions**

To protect the rights and welfare of participants, the study will be conducted in conformance with the Declaration of Helsinki, applicable FDA guidelines, the ICH E6 guidelines on Good Clinical Practice (GCP), and/or the laws and regulations of the participating country, whichever affords the greater protection to the human participant.

All investigators, sub-investigators and study personnel are required to read and follow the protocol, as well as any literature that accompanies the products prior to conducting the study procedure for the first time. All investigators participating in this study will be required to be trained in the proper use of the study procedures and in the components of this protocol by the sponsor.

The PI is ultimately responsible for the conduct of this study; however, he/she may designate a member of his/her staff to assist with the collection of data and completion of CRFs. The designee(s) will be documented on an authorization form that is signed by the PI and kept in the Regulatory Binder, to be updated as necessary.

Obtaining informed consent in accordance with national policy is mandatory for participant participation. All participant data is kept confidential and procedures will be implemented to ensure that participant confidentiality is not compromised. If alternative consent materials are used, they must be approved by Obstetrix CRE and the IRB at the clinical site prior to use. Documentation of the approved informed consent must be provided to Obstetrix CRE prior to study commencement at the clinical site.

After Informed Consent has been obtained, all screening procedures have been performed, and eligibility for the study has been confirmed, the participant will be considered enrolled in the study. After this point, the reason(s) must be documented on the CRF for any participant who withdraws, or for any reason cannot complete this study.

